**Outcome 2C):** Mean increase in maximum resting pressure by at least 50%.

**Objective 3) LUT, bowel and sexual functions (long-term TCSCS):** To test whether targeted long-term TCSCS (6-week trial) is safe and can improve urinary and faecal continence in humans with chronic SCI.

**Objective 3A)** To test whether targeted long-term TCSCS can improve urinary and faecal continence.

**Hypothesis 3A)** Long-term TCSCS will improve urinary and faecal continence. These improvements will be greater in individuals who complete intensive long term TCSCS compared to individuals who complete moderate long term TCSCS.

**Outcome 3A):** Mean decrease in the frequency of urinary and faecal incontinence by at least 50%.

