### Statistical Plan

Statistical analysis on LUT, bowel and sexual function will be performed (n = 40 with SCI).

A sample size calculation was performed using G\*power, version 3.0.10, with power set at 0.8 and  $\alpha$  at 0.05. Data from participants that match our inclusion criteria (n = 5, level of lesion C5 – T10, motor-complete AIS, A or B) were used from a recent TCSCS study. A minimum sample of 26 participants is required to detect a significant change in voiding efficiency [voided volume / (voided volume + post-void residual volume)] with short-term TCSCS (stim-off =  $37.8 \pm 40.6\%$  vs. stim-on =  $58.2 \pm 39.4\%$ , effect size = 0.510). Presently, there are no long-term TCSCS data with LUT and bowel outcomes, consistent with those proposed in this protocol, to facilitate a meaningful power calculation. Therefore, given this is a pilot trial study, and in order to account for drop out with long-term TCSCS, we aim to investigate 40 individuals with SCI (n = 40, C5 – T6). Short-term TCSCS effects on UDS parameters (AIM 2A) as well as ARM testing (AIM 2C) with or without different stimulation configurations will be assessed using a repeated measures non-parametric analysis of variance (ANOVA), i.e. Kruskal–Wallis test. Data from the repeatability portion of the study (AIM 2A) will be assessed within (same session) and between (different sessions) visits (2 and 3) using a repeated measures non-parametric ANOVA. TNFBM will also be assessed using a repeated measures non-parametric ANOVA.

Long-term TCSCS: Differences in continuous variables for questionnaire data (NBSS, NBD Score, I-QoL, IIEF-15 or FSFI) in AIM 3 will be assessed using a two-way repeated measures [baseline, immediately post long term TCSCS as well as post-interventional follow up at 6 and 12 weeks] ANOVA comparing changes between moderate and intensive TCSCS. Furthermore, UDS testing as well as 'faecal continence severity' (baseline and end of TCSCS 6-week period) will be assessed using Wilcoxon signed-rank tests within

groups. A P-value less than 0.05 will be considered statistically significant. A complete thematic analysis will be performed to collect contextual qualitative data from the sexual health interview.

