### *Low Urinary tract assessments*

- Neurogenic Bladder Symptom Score (NBSS): comprises 23 questions covering 3 domains, including incontinence (primary outcome, AIM 3A), storage & voiding, and specific consequences, as well as one question on QoL.
- The Incontinence-QoL (I-QoL): comprises 10 questions covering 3 domains, including avoidance and limiting behaviour, psychosocial impacts, and social embarrassment, which will be summarised as a total score. All scores, for each domain and a total, will be transformed into a continuous scale value.

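### Objective 3 claims that intensive TCSCS beats moderate, but faecal continence severity is tested only within each dose group, and the questionnaire analysis does not use the named primary domain or say which visit decides

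*Protocol*

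**What the plan says.** Hypothesis 3A (Objectives, Hypotheses and Outcomes) has two parts, improvement and greater improvement with the higher dose: "Long-term TCSCS will improve urinary and faecal continence. These improvements will be greater in individuals who complete intensive long term TCSCS" than in those who complete the moderate schedule. Hypothesis 3B has the same two parts for sexual function. Hypothesis 3C says that benefit lasts longer after intensive stimulation.

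The matching outcomes are not dose contrasts. Outcome 3A is a mean fall of at least 50% in urinary and faecal incontinence frequency. Outcome 3B is a mean improvement in satisfaction with sexual life. Neither names a comparison group or a visit. Outcome 3C names 6 and 12 weeks after cessation and ranks neither.

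The Statistical Plan puts NBSS, NBD Score, I-QoL and IIEF-15 or FSFI through a two-way repeated-measures analysis over baseline, immediately post-treatment, "as well as post-interventional follow up at 6 and 12 weeks] ANOVA comparing changes between moderate and intensive TCSCS". Urodynamics and faecal continence severity are compared between baseline and the end of the 6-week period by Wilcoxon signed-rank tests within groups. One rule covers everything: "A P-value less than 0.05 will be considered statistically significant".

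The description of the NBSS under Low Urinary tract assessments lists its domains, "including incontinence (primary outcome, AIM 3A), storage & voiding, and specific consequences". The Statistical Plan mentions neither this domain nor its primary status.

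**The concern.** Both long-term groups receive stimulation, 12 or 30 sessions. A pre-post change within a group therefore mixes any effect of stimulation with expectation and regression to the mean, and it says nothing about whether the dose matters. The dose comparison is the only concurrent contrast in Objective 3.

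For faecal continence severity that contrast is not planned. If one group's Wilcoxon test falls below 0.05 and the other's does not, the result may be read as a dose effect. If both do, it may be read as success for Hypothesis 3A as a whole. Neither reading tests the dose part of the hypothesis.

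For urinary continence the right kind of test is planned, but its link to the named primary outcome is missing. The interaction pools three post-baseline visits, whereas 3A concerns the effect of the 6-week course and 3C concerns persistence. Several scales and visits could then be offered as the answer to 3A.

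**Working it through.** **The plan's only computed figure.** "A minimum sample of 26 participants is required to detect a significant change in voiding efficiency", with "effect size = 0.510" and power 0.8. Mean difference 58.2 − 37.8 = 20.4; SD = √((40.6² + 39.4²)/2) = 40.0; 20.4/40.0 = 0.510. An exact paired t-test at one-sided 0.05 needs n = 26 (power 0.812), which reproduces the figure. Two-sided, it needs 33, and 26 gives power 0.705. The calculation concerns a short-term, within-person change, so it does not bear on a between-dose contrast. The plan says of the long-term part: "Presently, there are no long-term TCSCS data with LUT and bowel outcomes".

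**Hypothesis, outcome and test side by side.**

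| Item | Hypothesis | Outcome as worded | Planned test |
|---|---|---|---|
| 3A urinary | improves; intensive better | pre-post fall of at least 50% | NBSS (domain unstated), group by time, four visits |
| 3A faecal | improves; intensive better | pre-post fall of at least 50% | faecal severity: Wilcoxon within groups; NBD Score: group by time |
| 3B sexual | improves; intensive better | pre-post improvement | IIEF-15 or FSFI, group by time |
| 3C persistence | lasts longer with intensive | maintained at 6 and 12 weeks | questionnaires: same four-visit analysis; faecal severity: none |

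The modified Wexner score (WIS) is collected at baseline, week 13, week 19 and week 25, so data for a between-dose faecal comparison will exist. The NBD Score does enter the group-by-time analysis, but it combines constipation with incontinence.

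**Why two within-group tests are not a dose test.** Suppose both groups have the same true change and each within-group test has probability p of significance. The chance that exactly one group is significant is 2p(1 − p):

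- p = 0.05 (no change in either group): 2 × 0.05 × 0.95 = 0.095
- p = 0.80: 2 × 0.80 × 0.20 = 0.32
- p = 0.50 (the maximum): 0.50

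An apparent dose difference can therefore arise up to half the time when there is none.

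**Time effect against interaction.** Assume 20 per group, visit correlation 0.5, and an equal 0.5 SD improvement in both groups at all three later visits. The visit means 0, 0.5, 0.5, 0.5 have a sum of squared deviations of 0.375² + 3 × 0.125² = 0.1875. The noncentrality is 40 × 0.1875/0.5 = 15 on 3 and 114 degrees of freedom, which gives power of about 0.91 for the time effect. Simulation gave 0.92 for time and 0.05 for the interaction. The two effects answer different questions and must not be interchanged.

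**False-positive chance over the questionnaires.** For k independent tests it is 1 − 0.95^k. The protocol does not fix k:

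| Count | k | Chance |
|---|---|---|
| five group-by-time tests | 5 | 22.6% |
| five, plus four Wilcoxon (two variables, two groups) | 9 | 37.0% |
| all three ANOVA effects on five scales | 15 | 53.7% |
| five, plus 14 Wilcoxon (six urodynamic parameters and faecal severity, two groups) | 19 | 62.3% |

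For the five interactions alone, null simulations gave 15% to 23% as the assumed between-scale correlation fell from 0.7 or 0.8 to 0. The last row borrows the six parameters of Outcome 2A; the long-term sentence says only that urodynamic testing will be analysed. IIEF-15 and FSFI are sex-specific, so each participant contributes to four scales.

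**What the between-dose contrast can detect.** With a two-sample t-test, two-sided 0.05, power 0.80 and 20 per group (assumed, because the allocation ratio is not stated), the detectable difference is about 0.91 SD of the change score. With 16 per group it is 1.02 SD. For a difference of 0.51 SD, power with 20 per group is about 35%.

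**The case against.** A reader might infer that Objective 3 names no deciding effect at all. The documents do not support that. Comparing changes between doses is in substance the group-by-time effect, and a primary outcome for Aim 3A is named. Nor are time points wholly absent: the faecal and urodynamic tests are fixed at baseline and end of treatment, and 3C at 6 and 12 weeks. What is open is narrower: which NBSS domain is analysed, and which visit decides.

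A reader might also attach one error rate to the plan, such as 35%. That corresponds to about 8.4 independent tests (ln 0.65 / ln 0.95), a count that the protocol nowhere sets.

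Hypothesis 3A has two sentences, and a time effect does bear on the first. That stands, subject to the lack of an unstimulated group. It does not help the second.

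Finally, the long-term part is described as a pilot and proof of concept, and alpha splits or test hierarchies may properly sit in an analysis plan that is not shown. That stands too, so the absence of a formal hierarchy is not the complaint. The mismatch lies within the protocol: it states the dose hypotheses, the primary domain and the tests, and these do not fit together.

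**Conclusion.** The point holds in this limited form. The planned analysis of faecal continence severity cannot answer the dose part of Hypothesis 3A, even if followed exactly. This rests on the wording alone and needs no assumption. The NBD Score offers a partial between-dose look at bowel function, but not at faecal incontinence separately.

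For the questionnaires, the analysis is of the right kind but is not tied to the primary domain or to a visit. Read as five interaction tests, it has about a 15% to 23% chance of at least one false positive, assuming 20 per group and between-scale correlations from 0.8 down to 0. The range widens to about 62% if more tests are counted. The documents support neither a single headline rate nor the claim that the dose comparison is missing altogether.

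This is a moderate defect of specification that should be corrected before the data are analysed.

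**What to change.** In the Statistical Plan, long-term part:

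1. State that the dose claim in Hypothesis 3A is judged by the moderate-versus-intensive difference in change from baseline to the immediate post-TCSCS visit (week 13) in the NBSS incontinence domain, the outcome already called primary.
2. For the faecal dose claim, replace the within-group Wilcoxon test by a between-group comparison of change in a faecal score, for example the WIS. Use the week-19 and week-25 values for 3C.
3. Report time main effects and within-group tests as descriptive, with estimates and confidence intervals, and not as evidence of a dose difference.

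A formal fixed sequence is optional in this pilot; gating later contrasts on an underpowered first test has its own cost.

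The change needs no extra visits or data. The price is candour about precision: with 80% power only for about 0.9 SD at 20 per group, dose claims will often be inconclusive, and isolated within-group results become hypothesis-generating.

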## Participants

### Enrollment Goal

40 participants with SCI.

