### *Visits 4,5,6: Urodynamics and Anorectal Manometry – Weeks 4-6:*

Approximately 2.5 hours per visit.

Following Visits 1 (Screening) Visit 2 (baseline assessments) and Visit 3 (mapping visit) using a randomized counter-balanced approach, all individuals will be allocated into two distinct pathways:

- Pathway #1: individuals will start with Urodynamics, (UDS 1, Visit 4), followed by a second session of Urodynamics (UDS 2, Visit 5), and ARM (Visit 6).
- Pathway#2: individuals will start with ARM (Visit 4), followed by Urodynamics (UDS 1, Visit 5), and a second session of Urodynamics (UDS 2, Visit 6)).

TCSCS and Cardiovascular monitoring will be performed during UDS and ARM. Please see Description of Assessments for details of Urodynamics, ARM, TCSCS and Cardiovascular monitoring.

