### *Visits 7 – 18 or 36: Long Term TCSCS – Weeks 7-12:*

Approximately 90 minutes per visit.

Participants will come to ICORD for long term TCSCS, either 2 days/week (moderate) or 5 days/week (intense) for 6 weeks for a total of either 12 sessions or 30 sessions. Please see Description of Assessments for the details of an individual session.

During the 6 weeks of long term TCSCS, TNFBM will be measured during participants' conventional bowel routines at home. Participants will be asked to record the time from 'suppository insertion' to 'when bowel evacuation is completed' once per week for the bowel movement completed mid-week during each week of the 6 week TCSCS pathway.

24 ABPM will be performed mid-way through the 6 weeks and during the final week of the 6 weeks of treatment in combination with the participants' bowel routine.

## Visit 19-20 OR 37 – 38: Immediate Post-TCSCS Assessments – Week : 13

Visit 19 or 37 (approximately 3 hours):

After the 6 weeks of TCSCS, all participants will complete 1 visit at ICORD including UDS assessments and a SCI severity assessment (ISNCSCI). Please see description of Assessments for details.

Visit 20 or 38 (approximately 1 hour):

A series of questionnaires on low urinary tract function, bowel function, cardiovascular function and sexual health will be conducted by telephone or video conference call (considering the present COVID-19 pandemic environment). The questionnaires are listed below and details can be found in the Description of Assessments Section.

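### The four-visit repeated-measures ANOVA for moderate versus intensive TCSCS should give way to a baseline-adjusted mixed model on all available post-baseline questionnaires

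*Protocol*

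**What the plan says.** The long-term paragraph of the protocol's Statistical Plan covers "Differences in continuous variables for questionnaire data (NBSS, NBD Score, I-QoL, IIEF-15 or FSFI) in AIM 3". It assigns them a two-way repeated-measures "ANOVA comparing changes between moderate and intensive TCSCS". The time factor has four levels: "baseline, immediately post long term TCSCS as well as post-interventional follow up at 6 and 12 weeks".

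The same section chooses 40 participants, partly "in order to account for drop out with long-term TCSCS". It states no dropout rate. Enrollment Goal repeats the total: "40 participants with SCI".

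The schedules are "either 2 days/week (moderate) or 5 days/week (intense) for 6 weeks for a total of either 12 sessions or 30 sessions". The protocol gives no allocation ratio or method for them. The only randomisation it describes concerns the order of urodynamics and manometry: "using a randomized counter-balanced approach, all individuals will be allocated into two distinct pathways".

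The post-baseline questionnaires fall at week 13 (after stimulation has ended) and at weeks 19 and 25. Urodynamics and faecal continence severity are outside this ANOVA; they are tested within groups by Wilcoxon signed-rank tests.

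**The concern.** This ANOVA is the only between-group analysis that the protocol specifies for the long-term phase. Hypotheses 3A to 3C each claim more benefit from the intensive schedule. Two features of the named method serve those claims poorly.

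- **Complete rows.** Classical repeated-measures ANOVA needs all four values. A participant who misses only the week-25 call would lose the week-13 and week-19 data as well. The plan expects dropout, and the two latest visits are the ones that answer Hypothesis 3C.
- **Baseline as an outcome level.** With two groups and four times, the interaction tests any difference in profile, on 3 degrees of freedom. It names no contrast at a given visit, and it does not use baseline to reduce residual variance.

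At stake is precision in a small study, and a clear estimate for each hypothesis.

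**Working it through.** **Inputs from the protocol.** Total 40; two schedules; four time points, three of them post-baseline; alpha 0.05.

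**Assumptions, because the protocol is silent.** 20 per group; dropout rates; the correlation ρ between baseline and later scores; the effect size.

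**The plan's own figure.** The one computed figure is the minimum of 26 for the short-term change in voiding efficiency (effect size 0.510, power 0.8). A one-sided paired t-test gives n = 26 (power 0.812); a two-sided test gives 33. This figure does not concern the long-term comparison, for which there is no calculation.

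**1. Degrees of freedom.** Group-by-time: (2 − 1) × (4 − 1) = 3. A named contrast at one visit has 1.

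**2. Baseline adjustment with no dropout.** For one visit with common variance σ²:
- change score: 2σ²(1 − ρ)
- adjusted for baseline: σ²(1 − ρ²)
- ratio: (1 − ρ²) / [2(1 − ρ)] = (1 + ρ)/2

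This gives 0.75 at ρ = 0.5 and 0.85 at ρ = 0.7. At 20 per group, two-sided 5% and 80% power, the detectable difference falls from 0.909 to 0.787 SD at ρ = 0.5, and from 0.704 to 0.649 SD at ρ = 0.7.

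**3. Participants kept.** Completers = 40 × (1 − d) for overall dropout d. The mixed-model row counts anyone with at least one post-baseline visit. It comes from a simulation in which only about a third of dropouts left before the first such visit.

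| Overall dropout | 10% | 20% | 30% |
|---|---|---|---|
| All four values | 36 | 32 | 28 |
| Mixed model | 38.6 | 37.1 | 35.6 |

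If every dropout happened during stimulation, the mixed model would also have 36, 32 and 28. If instead 5, 10 or 15% missed each post-baseline visit independently, completers would be 40 × (1 − m)³ = 34.3, 29.2 or 24.6.

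**4. Simulated power.** 1,000 trials per setting; 20 per group; ρ = 0.6 between all visits; a constant 0.7 SD effect after baseline; dropout completely at random.

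| Dropout | 0% | 10% | 20% | 30% |
|---|---|---|---|---|
| ANOVA interaction, completers | 0.71 | 0.62 | 0.59 | 0.53 |
| 1-df change contrast, completers | 0.85 | 0.80 | 0.74 | 0.70 |
| Baseline-adjusted mixed model | 0.93 | 0.91 | 0.91 | 0.88 |

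The second row is the fair comparator for the third, since both test one contrast. Both average the three post-baseline visits, so single-visit contrasts would have less power than shown. Type I error of the mixed model was 0.04 to 0.06.

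**5. Source of the gain.** A separate simulation with 16 completers per group (20% dropout) gave 0.75 for the change contrast and 0.87 for the baseline-adjusted contrast on the same people. The mixed model on all available visits reached 0.91 at that dropout. Adjustment therefore supplies most of the gain over the change contrast, and retained partial data the rest.

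**The case against.** The strongest reply is that the protocol names an ANOVA and says nothing about discarding anyone. Missing-data rules and contrasts commonly go into a statistical analysis plan, and that document is not at hand. This stands in part. A reader might infer that the protocol prescribes deletion of incomplete participants, or contradicts itself by expecting dropout. It does neither; complete rows are a property of the classical method. The named method is nevertheless a stated choice, and its handling of baseline is open to criticism whatever the missing-data rule.

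Other stronger readings also fail:

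- **The mixed model rescues all the expected dropout.** The first post-baseline questionnaire comes after stimulation ends. Anyone lost before it contributes nothing to the proposed model either.
- **The ANOVA is biased because the schedules differ in burden.** Unequal dropout is plausible but undocumented. Dropout that depends only on schedule does not bias the contrast, and dropout that depends on unobserved response would bias both methods. Only dropout related to observed post-baseline values favours the mixed model.
- **All of Hypotheses 3A to 3C rest on this test.** Faecal continence severity is analysed outside it.
- **The trial is underpowered against a target.** This is a pilot that sets no long-term power target.

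Hypotheses 3A and 3B speak of people who complete stimulation, which may seem to justify a completer analysis. But completing stimulation is not the same as answering all four questionnaires.

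**Conclusion.** The point holds as an inexpensive improvement to a stated method, not as an error that invalidates the plan. The main gain is from baseline adjustment and targeted contrasts: single-visit variance is about 0.75 to 0.85 of the change-score variance for ρ of 0.5 to 0.7, with or without dropout. Keeping partial follow-up adds less, and adds nothing if all losses occur during stimulation. The completer counts and simulated powers are illustrative; they rest on the assumed equal groups, dropout, correlation and effect. They do not carry over to IIEF-15 and FSFI, where the sample splits by sex. Because the protocol does not say that the schedules are randomised, a reader might take baseline adjustment as protection against confounding. If allocation is not random, adjustment improves precision but does not remove confounding.

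**What to change.** In the long-term paragraph of the Statistical Plan, replace the two-way repeated-measures ANOVA with a linear mixed model:

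- **Outcomes:** the post-treatment, 6-week and 12-week scores, using all available post-baseline visits.
- **Fixed effects:** group, visit, group-by-visit and baseline score, with within-participant correlation modelled.
- **Inference:** a small-sample degrees-of-freedom correction such as Kenward-Roger.
- **Contrasts, each with a 95% CI:** the post-treatment group difference for the questionnaire outcomes of Aims 3A and 3B; the 6- and 12-week differences for Aim 3C.
- **Stated limits:** data are assumed missing at random, and participants with no post-baseline questionnaire do not contribute.

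The cost is the rewording of one paragraph. Standard software suffices, and no participant, visit or measurement is added. The price is the missing-at-random assumption and the degrees-of-freedom correction.

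### Long-term urodynamics and faecal continence severity are tested only inside each dose group, so neither the overall effect nor the dose contrast is tested for these two outcomes

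*Protocol*

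**What the plan says.** The aim under Objective 3A is "To test whether targeted long-term TCSCS can improve urinary and faecal continence". Hypothesis 3A repeats this and then adds a second claim, that the improvement is larger after intensive than after moderate stimulation. Under the long-term visits (Visits 7 to 18 or 36), both groups receive active stimulation, on 2 or 5 days a week for 6 weeks (12 or 30 sessions). No allocation ratio is given for the two doses.

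The Statistical Plan sends the long-term outcomes down two routes:

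- NBSS, NBD Score, I-QoL and IIEF-15 or FSFI go into a two-way repeated measures ANOVA with four time points and both dose groups.
- UDS and faecal continence severity are handled differently: "baseline and end of TCSCS 6-week period) will be assessed using Wilcoxon signed-rank tests within" groups. The groups in the preceding sentence are moderate and intensive.

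The same section says "we aim to investigate 40 individuals with SCI (n = 40, C5 – T6"), and sets the threshold: "A P-value less than 0.05 will be considered statistically significant". It states that there are no long-term data for a meaningful power calculation and calls the trial a pilot.

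**The concern.** For these two outcomes the plan fixes a test that answers neither question in Objective 3A. Whether long-term stimulation changes the outcome is a question about everyone stimulated, but it is put twice, each time to part of the sample. Whether intensive is better than moderate needs a direct comparison of change between doses, and none is stated. Setting one within-group p-value beside another does not supply it.

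The practical risk is a split result. If both doses work equally well and each test has only moderate power, one significant and one non-significant group is a common outcome. It could then be read as support for the dose claim in Hypothesis 3A.

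The two outcomes carry weight. Faecal incontinence is half of Outcome 3A. UDS is the only laboratory measure of bladder or bowel function listed after treatment; the other bladder, bowel and sexual measures at that stage are questionnaires or a time recorded at home.

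**Working it through.** **Inputs.** From the Statistical Plan: significance level 0.05; "with power set at 0.8 and" α at 0.05; "effect size = 0.510"; 40 participants. Not in the documents and therefore assumed: 1:1 allocation (20 per dose), two-sided testing, and a long-term effect equal to the short-term 0.51.

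**1. The plan's own figure.** "A minimum sample of 26 participants is required to detect a significant change in voiding efficiency". The difference is 58.2 − 37.8 = 20.4, the root mean square of the two SDs is √((40.6² + 39.4²)/2) ≈ 40.0, and 20.4/40.0 = 0.51. Used as a paired standardised effect, this implies a correlation of about 0.50 between the two conditions. A paired t-test with the exact noncentral t gives:

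- one-sided 0.05: n = 26, power 0.812, which reproduces the stated minimum;
- two-sided 0.05: n = 33.

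The plan does not state the sidedness. On either reading a group of 20 falls below the minimum for this effect, and all 40 exceed it.

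**2. Power of the stated test against one test in everyone.** The signed-rank test is approximated by a t-test with effective sample size 0.955 × n and noncentrality 0.51 × √(0.955 n), and checked by simulating the test itself on normal data.

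| Effect 0.51 at both doses | One dose group | All participants |
|---|---|---|
| Two-sided, 20 and 40 | 0.56 (simulated 0.557) | 0.87 (simulated 0.871) |
| One-sided, 20 and 40 | 0.69 | 0.93 |
| Two-sided, 20% dropout assumed, 16 and 32 | 0.46 | 0.78 |

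The protocol mentions dropout but gives no rate, so the last row is illustrative. At other common effects, simulated two-sided power for 20 and 40 is 0.22 and 0.44 at 0.3 SD, and 0.82 and 0.99 at 0.7 SD. The effect detectable with 80% power is 0.68 SD at 20 and 0.465 SD at 40.

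**3. Chance of a split result when both doses work equally.** With power 0.56 in each of two independent groups:

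- exactly one significant: 2 × 0.56 × 0.44 ≈ 0.49;
- both significant: 0.56² ≈ 0.31.

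**4. What happens if the doses differ.** Intensive effect fixed at 0.51, 20 per group, two-sided, simulated:

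| Moderate effect | Intensive group alone | All 40 pooled |
|---|---|---|
| 0.51 | about 0.56 | 0.87 |
| 0.25 | about 0.56 | 0.62 |
| 0.15 | about 0.56 | 0.51 |
| 0 | about 0.56 | 0.32 |

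Pooling helps clearly when the doses act alike, helps little at a moderate effect of 0.25, and loses power when the moderate dose does almost nothing.

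**The case against.** A reader might infer that the main question of Objective 3 is answered with half the enrolled sample. The documents do not support that. Under Validated questionnaires, the NBSS incontinence domain is named as the AIM 3A primary outcome, and the NBD Score is described as covering faecal incontinence. Both are in the two-way ANOVA, whose time effect uses both dose groups. UDS is not listed among the Objective 3 outcomes; its parameters are Outcomes 2A and 2B. No data are discarded either, since each half is analysed.

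The strongest counter-argument is about dose. Hypothesis 3A expects intensive stimulation to do better, and under a marked dose effect the last table shows that a pooled test can be weaker than the intensive group alone. Dose-specific results are then a reasonable thing to want. This stands, and it is why the remedy should carry dose in the analysis instead of pooling and ignoring it. It does not rescue the current wording, which tests no dose difference for these outcomes.

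Other points stand in part. The 0.51 is a short-term stim-on against stim-off effect from five people, so the power figures illustrate the scale and do not predict. It is also tempting to charge the two tests with a false-positive rate of 1 − 0.95² = 9.75%. That applies only if success means either group being significant, and the protocol states no such rule. Finally, a statistical analysis plan that is not shown could add a pooled test. But the protocol has not left this open: it names the test and the level at which it is applied.

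**Conclusion.** The point holds for two outcomes only, long-term UDS and faecal continence severity. For these the stated analysis covers neither the overall effect nor the dose contrast. At the borrowed effect of 0.51, equal at both doses, and with 20 per group, testing by dose gives about 56% power against about 87% in all 40. It also gives roughly an even chance that just one dose is significant. These figures rest on 1:1 allocation, two-sided testing and a long-term effect that the protocol does not give. The power advantage disappears if the moderate dose has little effect, but the missing dose comparison remains a gap at any effect size.

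The conclusions on the named AIM 3A primary outcome are not at risk. This is a cheap improvement, not a flaw in the main analysis of Objective 3.

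**What to change.** For UDS and faecal continence severity, replace the separate within-group tests by one analysis of all participants with dose as a factor. Two forms would serve:

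- a model with time, dose and time-by-dose, in line with the questionnaire analysis; or
- if ranks are preferred, a signed-rank test of change stratified by dose, plus a rank-based comparison of change between the doses.

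Report the overall change and the between-dose difference, each with a 95% confidence interval. Keep the within-dose changes as descriptive results, and say that a significant result in one dose and not the other is not evidence of a dose effect.

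The cost is wording in the Statistical Plan; the baseline and end-of-treatment data are already collected. The small downside is that the overall estimate averages over two doses, which the by-dose results and the dose term make visible.
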